Culturally specific healthcare services that are led and delivered by Indigenous peoples can have a key role in improving quality of healthcare and treatment access.^20^ Aboriginal Community Controlled Health Services (ACCHSs) provide accessible and culturally appropriate healthcare to Indigenous communities across Australia. Each ACCHS has its own holistic service delivery model for the communities that they serve.^20^ As with mainstream (general population) services, knowledge and practice of screening and brief intervention vary between and within Indigenous primary care services.^13 21 22^ Some ACCHSs have an alcohol and other drug (AOD) worker or team, or links with external AOD specialists/services. Others may have no specific AOD expertise and health practitioners may lack confidence in delivering alcohol care (ie, screening, brief intervention, counselling or medicines). Prior to 2017, the Australian government had asked ACCHS staff to record clients’ alcohol use as ‘safe’ or ‘unsafe’, ‘non-drinker’ or ‘ex-drinker’.^22^ However health practitioners may or may not have known current drinking guidelines or have applied these to assess the risk.

To increase standardisation of alcohol screening in ACCHSs, in July 2017 the use of the Alcohol Use Disorders Identification Test-Consumption (AUDIT-C) was added as a national key performance indicator for ACCHSs.^23^ AUDIT-C^24^ is a 3-item screening tool, comprised of the first three questions of the 10-item AUDIT.^25^ This short form has been shown to have good sensitivity and specificity in comparison to the full AUDIT.^24^ Several studies suggest that AUDIT-C is valid in Indigenous primary care settings, though further study into culturally appropriate delivery is suggested.^26–28^

Internationally, research suggests that support can help primary care services increase implementation of alcohol screening and brief intervention^29^ or provision of pharmacotherapies for relapse prevention in alcohol dependence.^19^ Support which is multi-faceted, and targets several areas of a health service seems particularly promising.^29^ For example the approach may target not just doctors, but other professionals, clients, and organisational systems.^29^ Continuing quality improvement approaches may offer sustainable benefit, including in ACCHSs.^30^ However there have been very few studies of culturally relevant support models for ACCHSs in alcohol care,^21 30^ with even fewer conducted by Indigenous researchers.

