This paper outlines the trial protocol for testing if a model of support can assist ACCHSs to integrate the mainstream evidence base on alcohol care with their own cultural and clinical expertise. The use of an inactive control group can be challenging on ethical and partnership grounds, particularly for vulnerable communities. In contrast, a wait-control design allows support to be delivered to all participating ACCHSs.

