### The model of support

ACCHSs will be acknowledged as the experts in cultural healthcare for Indigenous peoples in their communities and Australia. The study also recognises the need for flexibility based on needs of individual services and of the ACCHS sector as a specialist sector overall. Support approaches will include the same core elements (table 1). However, approaches will be tailored to the needs of each ACCHS, for what works best for their service, clients and communities.

The core support elements were designed based on evidence-based approaches for supporting implementation of alcohol care.^21 29^ The project team also drew on their experience working within (six authors) and with Aboriginal health services; and in health workforce development (nine authors). Advice was also received from ACCHS peak organisations and networks in New South Wales and South Australia, and from a research team conducting a quality improvement trial for ACCHSs on diabetes screening.^42^

At the start of the early support phase, the support will be refined based on preliminary analysis of qualitative data from staff interviews and after feedback from the initial national workshop for early support service representatives. Tailoring and further minor refinement of support will occur during the trial, informed by service feedback.

Early support (‘intervention’) services will receive the support soon after the trial starts (1 year of active support, 1 year maintenance phase). Late support (wait-control) services will receive the same intervention elements 2 years after the start of the early-support phase. Due to the nature of the intervention, it is not possible to blind participants or staff as to which services are receiving support.

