WorkshopsA national workshop will be held at the beginning of each support phase to bring champions from those services together for capacity building and networking. Feedback will be obtained from champions about pre/post-workshop knowledge, training preferences, priority areas for support and useful resources. Key presentations from workshops will be video-recorded and made available via a password-protected website.A wrap-up workshop will be organised for early support service champions (only) at the end of their support phase. Opportunities will be provided for service champions to provide verbal and written feedback on support, to discuss continuing quality improvement approaches and to network. Study results to that point will be discussed.Onsite trainingTraining will be offered at each service for all staff, with maximum duration of 2 days. Core elements will include screening, alcohol and the body, brief intervention and treatment approaches, including relapse prevention medicines. Due to the individuality of each service, flexibility will be given to allow inclusion of other (alcohol-related) training topics. The training will be co-facilitated by an addiction specialist (KC) and an Aboriginal researcher with clinical background ([name]) and will use culturally specific content and resources. Training content will be aligned with Indigenous protocols such as gender appropriateness, kinship systems and cultural obligations; such a family and community sharing which at times can impact on substance use.^27 44^ Pre/post-training feedback will be collected from participants.Resources/fundingThe trial will provide several hard copy and electronic resources for free to services (ie, the Handbook for Aboriginal Alcohol and Drug Work,^45^ Alcohol Awareness Kit^46^ and Quick Reference Guide to the Treatment of Alcohol Problems^47^).Each ACCHS will be provided with funding to purchase additional resources. Services can choose, in partnership with the chief investigators, how they spend their funding. The early support arm of the project will receive up to $9000 for resources. The late support arm will receive up to $3500. This is a reduced sum as they will have access to resources developed within the early support phase, so time and development costs will be less. Resources must be alcohol-related and may include additional training, conference attendance, education resources for staff or clients, funds for health promotion events or for local adaptation of resources.Practice software supportA Communicare support officer will be available during the trial to support ACCHSs with the practice software. Some ACCHSs may choose to make modifications to Communicare to make alcohol ‘clinical items’ more accessible for staff. One example is adding AUDIT-C into the Aboriginal and Torres Strait Islander (Indigenous) health assessment (‘Adult Health Check’), which was not routine in standard versions of Communicare at the time of trial commencement. AUDIT-C can also be added to other regular assessments such as antenatal and the pre-consult examination (ie, routine observations and/screening by a nurse or Aboriginal health worker before seeing the doctor). Services will also be provided with information about existing fields (‘clinical items’) available on Communicare for recording episodes of alcohol care (education/advice; on-site counselling), which can then be retrieved by data extraction.Second monthly data feedbackIndividual services will receive feedback on their routinely collected data on alcohol care every 2 months during their support phase. Data will be represented visually using images and or graphs (figure 3) and be fed back to nominated staff, including champions. Services will be asked for feedback on the data representation early in the support phase and adaptions will be made as requested. Services will be encouraged to discuss the results among staff, to see if there are ways to further improve alcohol screening and treatment rates.Phone conferencesSecond monthly phone conferences will be organised for service champions. These will provide the opportunity for ACCHSs to network nationally. The champions will be split into two groups for the phone conferences, based on remoteness. During teleconferences, champions can discuss their data feedback, progress, successes, difficulties, helpful tools, resources or approaches.Online platformA password-protected web portal will allow ACCHS staff to access and share current evidence, culturally appropriate resources and to network. It will include a discussion board. Short videos, training presentation slides and clinical protocols will be uploaded by project staff.

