#### Quantitative

Only the routinely collected data on Indigenous Australian clients aged 16+ years who have attended a participating ACCHS in the last 12 months will be included in analysis to assess:

The odds of a client being screened using AUDIT-C at least once in any 2-month period (considering those who attend in that period).The odds of a client being recorded as receiving treatment for unhealthy alcohol use at the ACCHS, including advice/education or counselling, relapse prevention medicines.The number of clients identified by ACCHS staff to have unhealthy alcohol use:via AUDIT-C: using cut-offs recommended for ACCHSs by the Australian Institute of Health and Welfare (3+ for a woman, 4+ for a man).^23^
and/or staff perception of drinking status (eg, safe, unsafe, non-drinker or ex-drinker).

We will use statistical packages, IBM SPSS for descriptive analyses and R for multi-level modelling.

Multi-level modelling will be used to account for clustering of observations under clients, who are nested within services. We will assess if clients are more likely to be screened for risky alcohol-use and provided with treatment if they are attending a service receiving support.

Two dummy variables will be constructed to indicate whether or not clients were screened with the AUDIT-C during each 2-month data extraction period, or if they received treatment. These variables will be used as outcomes in multi-level logistic regressions. As data are aggregated at bimonthly intervals, repetitive screenings within those 2-monthly periods will not influence the modelled effect of the intervention. However, to ensure that the intervention is associated with increased odds of appropriate screening, we will create a dummy variable indicating whether a client has been screened in the previous 12 months, and use this variable as the outcome in a multi-level logistic regression.

Characteristics of ACCHSs, such as number of clients, will be compared descriptively between the early/late-support services. Characteristics that display major imbalance between arms will be considered as adjustment factors in outcome analyses. As data are collected as part of routine clinical activity, missing data are likely to be non-random, as such multiple imputation will not be performed.

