All analyses will be repeated for the maintenance phase of the study to see if study effects weaken or strengthen over time. The analysis will also be repeated after the late support services have received support, to see if any effect on use of screening or treatment can be replicated.

If a significant effect of the support on alcohol care outcomes is demonstrated, a secondary analysis will examine the elements of support which were most effective, and whether the effect of support changed over time during a support phase. Potential change in client health indicators over time (AUDIT-C scores, GGT, HbA1C, BP) will be examined in relation to support provision.

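### Repeating the analysis after late support has no unsupported concurrent arm, so it cannot show replication without a stated carry-over or calendar-time assumption

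*Protocol article*

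**What the plan says.** All places are in the protocol article.

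- **Introduction:** "a wait-control design allows support to be delivered to all participating ACCHSs". No service stays unsupported to the end.
- **The model of support:** early services start "soon after the trial starts (1 year of active support, 1 year maintenance phase"), and late services "will receive the same intervention elements 2 years after the start of the early-support phase".
- **Analysis, Quantitative:** the question put to the model concerns clients of a service that has support (the quote stops one word short): "We will assess if clients are more likely to be screened for risky alcohol-use and provided with treatment if they are attending a service receiving".
- **Same section, on year 2:** "All analyses will be repeated for the maintenance phase of the study to see if study effects weaken or strengthen over time".
- **Same section, on the late phase:** "The analysis will also be repeated after the late support services have received support, to see if any effect" on screening or treatment can be replicated. No comparator, calendar-time term or carry-over assumption is given for this repeat.
- **Introduction, on the measure itself:** "in July 2017 the use of the Alcohol Use Disorders Identification Test-Consumption (AUDIT-C) was added as a national key performance indicator for ACCHSs".
- **The model of support, on resources:** "The late support arm will receive up to $3500", against up to $9000 in the early arm.

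**The concern.** The trial's causal claim rests on comparing services that have support with randomised services that do not yet have it. That comparison is available for two years and ends when the late arm starts. After that, the early arm is a formerly supported group, and the late arm's only unsupported data lie in its own past.

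Replication implies that the late phase is a second test of the same standing as the first. A between-arm repeat could suggest failure precisely because the early effect lasted. A before-after repeat could suggest success because AUDIT-C use was rising anyway. Either could be reported as a finding about the support model.

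A smaller issue concerns the maintenance phase. A statement that effects weakened or strengthened needs an estimate of the change, and two analyses run separately and read side by side do not provide one.

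**Working it through.** **1. The protocol's own figure.** Inputs from the Sample size section: 60% versus 73%, 10 services per arm, 86 unhealthy drinkers per service, intra-cluster correlation 0.04, two-sided 0.05, 80% power.

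- Design effect: 1 + (86 − 1) × 0.04 = 4.4.
- Effective size per arm: 10 × 86 / 4.4 = 195.
- Power of the two-proportion z-test: 0.785 with unpooled variance, 0.779 with pooled variance.

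This is close to the stated 80%. The calculation sets a supported arm at 73% against an unsupported late arm at 60%, and the second of these no longer exists in the late phase. The 13 points refer to treatment provision. The protocol gives no planning effect for screening, so 13 is used below only as a scale.

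**2. Between-arm repeat.** Let *r* be the share of the early effect still present in the late phase. The protocol gives no value, so the range is shown. With a true late-arm effect of 13 points, the late-minus-early contrast is 13 × (1 − *r*). Power uses the inputs of step 1 (pooled variance).

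| *r* (assumed) | Contrast, points | Power |
|---|---|---|
| 0 | 13.0 | 0.78 |
| 0.25 | 9.75 | 0.54 |
| 0.5 | 6.5 | 0.29 |
| 0.75 | 3.25 | 0.11 |
| 1 | 0 | none beyond the test size |

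The Discussion hopes that the model will be sustainable. The practice-software support includes changes such as building AUDIT-C into the adult health check, which may well outlast active support. An *r* well above 0 is therefore what the authors are aiming for.

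**3. Before-after change in the late arm.** The estimate is the true effect plus the calendar-time change *s*. The documents give no *s*. For assumed values of 2, 5 and 10 points:

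- true effect 13: the estimate is 15, 18 or 23;
- true effect 0: the estimate is 2, 5 or 10.

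**4. Late-arm change minus the early arm's concurrent change.** This removes a calendar trend common to both arms, but it counts early-arm waning as late-arm gain. Suppose the early arm holds its full 13 points in year 2 and share *r* of it in the late phase. The late arm gains 13 and the early arm changes by 13*r* − 13, so the difference is 13 − (13*r* − 13) = 13 × (2 − *r*). That is 13 at *r* = 1, 19.5 at *r* = 0.5 and 26 at *r* = 0.

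**5. How the options relate.** If *C* is the late-phase contrast (late minus early) and *E* the year-2 effect (early minus late), the late-arm effect is *C* + *rE*. The plain contrast takes *r* = 0 (full wash-out), and the difference in changes takes *r* = 1 (full persistence). With *C* = 6.5 and *E* = 13, the late-arm effect lies anywhere from 6.5 to 19.5, depending on an *r* that the late-phase data do not identify without further assumptions.

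**The case against.** The protocol commits to neither a late-versus-early contrast nor a simple before-after change. Two-monthly data over five years, a 12-month baseline and a question framed around services receiving support all fit a single model with a time-varying support indicator and period effects. Such details are commonly left to an analysis plan. This stands, and it would be wrong to say that the protocol has specified a biased analysis. What remains is the stated purpose: no analysis plan can supply an unsupported concurrent arm, so any version of the repeat needs an assumption that the word replicated conceals.

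Four stronger readings are tempting, and the documents do not support them.

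- **That bias towards zero is certain.** It scales with persistence, which is not quantified, and vanishes under full wash-out.
- **That a national AUDIT-C trend is documented.** The Introduction reports one event, the July 2017 indicator, and no trend. Table 2 gives first enrolment as 28/10/2016. If early support began no earlier than that, late support began no earlier than late October 2018. The last unsupported year would then fall after the indicator came in. Gradual uptake could still be under way, but its size is unknown.
- **That the late arm receives a different intervention.** The protocol says the same elements are delivered. The lower funding is disclosed and explained by resources already developed, and the early arm's extra wrap-up workshop comes only at the end of maintenance. The funding difference deserves mention and no more.
- **That the maintenance analysis is invalid.** In year 2 the late arm is still unsupported, so the contrast is randomised. The protocol also plans to examine change over time during a support phase, though only if a significant effect is found first.

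**Conclusion.** The point holds in a limited form. Once the late services are supported there is no unsupported concurrent arm, and the planned repeat cannot carry the weight of a replication. On the 13-point planning scale, a between-arm repeat could show anything from 13 points to 0 for the same true late-arm effect, and 6.5 at an assumed 50% persistence. A before-after repeat adds the whole calendar-time change, of unknown size. The absence of a concurrent unsupported arm follows from the protocol's design. The sizes rest on assumed persistence and assumed secular change, and on applying the treatment-provision planning effect as a scale.

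This concerns a follow-on analysis. The main early-versus-late comparison before late support starts, the primary outcome and the sample size are untouched. It should be corrected because the correction is cheap and the late-phase claim would otherwise be overstated.

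**What to change.** 1. Fit one multi-level model over all phases, with calendar-period effects and a time-varying support or phase term by arm.
2. Estimate the late-arm effect from its change relative to its last unsupported year, under a stated carry-over assumption for the early arm. Show a sensitivity range from full persistence to full wash-out. Do not simply subtract the early arm's concurrent change, because that overstates the late effect if the early arm is waning.
3. Describe the result as non-randomised supporting evidence, drop the word replicated, and note the lower late-arm funding.
4. Keep the year-2 early-versus-late contrast. To say whether the effect weakened or strengthened, report the year-2 minus year-1 arm contrast with its confidence interval from the same model.

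No change to design, data extraction or sample size is needed. The cost is slightly more analysis work and a more modest claim for the late phase.

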### Ethics approvals

Ethics approval was obtained by eight ethics review committees, including three Aboriginal-specific committees. As there are minimal foreseeable risks in this study, there will not be an independent committee monitoring trial conduct, data or adverse events. Feedback from services will be provided to investigators and adaptations made as necessary.

### Patient and public involvement in the research

This trial was suggested by the Aboriginal Health Council of South Australia, the peak organisation for South Australian ACCHSs. Service participation in the trial must be approved by the board of each local ACCHS. The board is recognised as representing patients and community in such decisions. As described earlier, service staff will be consulted throughout their active support phase on how project support can best be tailored. Results will be fed back bimonthly to services in an accessible manner for all staff and board members, and services will have opportunity to provide comment on draft outcome reports before publication.

### Dissemination of findings

After feedback to participating ACCHSs, results will be disseminated via peer-reviewed publications and conference presentations. Publications will be led by study investigators, research students or staff supported by the investigators. The resources developed through this trial will also be made freely available electronically at the end of the study period to support other health services.

#### Data sharing

It is not possible to make the data set publicly available because of ethical constraints. Alcohol is a sensitive issue, and the data belong jointly to the 22 services who take part. For the main outcome report, statistical code used to analyse data will be made publicly available.

#### Authorship policy

All grant holders, and those involved in study conception and design, will co-author the main outcome piece. Further articles based on sub-analyses or secondary research questions will be authored by those directly involved in those questions. Acknowledgement will be given to individuals involved in design of the main paper.

### Protocol amendments

The trial’s registration data are shown in table 2. Any necessary protocol amendments will be agreed on by study investigators, and where appropriate, participating services. Then they will be registered with the Australian and New Zealand Clinical Trials Registry.

**Table 2 T2:** WHO trial registration data

Data category	Information
Primary registry and trial identification number	Australia New Zealand Clinical Trials Registry: ACTRN12618001892202
Date of registration in primary registry	21/11/2018
Secondary identifying numbers	APP1105339
Sources of monetary or material support	NHMRC, Australia
Primary sponsor	The University of Sydney
Secondary sponsor	Royal Prince Alfred Hospital
Contact for public and scientific queries	[name], FAChAM, FAFPHM, PhD [contact]
Public title	Supporting Aboriginal community controlled health services to deliver alcohol care: a cluster randomised controlled trial
Scientific title	Increasing uptake of evidence-based management of unhealthy alcohol use in Aboriginal primary healthcare services: a cluster randomised controlled trial
Counties of recruitment	Australia
Health condition(s) or problem(s) studied	Hazardous alcohol use; alcohol use disorders
Interventions	Health service support (including training, sharing learning between services); regular data feedback
Key inclusion or exclusion criteria	Health services: are Aboriginal Community Controlled Health Services deliver care to at least 1000 unique clients annually use ‘Communicare’ as their practice software Data from clients 16 years and older are eligible for extraction
Study type	Interventional; Allocation: randomised; Primary purpose: prevention; Cluster randomised trial
Date of first enrolment	28/10/2016
Target sample size	22 services
Recruitment status	Complete
Primary outcomes	AUDIT-C screening rate
Key secondary outcomes	Brief intervention for alcohol rate

AUDIT-C, Alcohol Use Disorders Identification Test-Consumption; NHMRC, National Health and Medical Research Council.

